### 6.6.1 Early Stopping of Follow-up

If the study is stopped prematurely for any reason, the participating PIPs, GP practices, care homes and residents will be informed.

### 6.6.2 Participant Transfers

If a participant moves from the care home where they have been recruited, they will be withdrawn, because it will not be possible for the intervention to be delivered elsewhere. The data collected until the time at which they withdrew from the study, will be held and used.

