### **6.1.3.1 PIPs**

If a PIP withdraws from the study, and a new PIP is not appointed within the 6 month study period, the care home and participating residents will be informed that the PIP intervention is no longer taking place, but that the data will be collected for individual resident participants at standard data collection times and may still be used in the final analysis.

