### **6.1.3.3 Care home associated with the consented GP practice.**

In the event a care home withdraws participation (or becomes ineligible e.g. following a regulatory inspection) within the first month of resident recruitment, the local research team will ask the GP practice to suggest another care home if possible. The care home will be made aware that data collected on the care home and residents of that care home to date cannot be erased and may still be used in the final analysis. Residents will be advised, by the research team, that their care home has withdrawn and they can no longer take part in the study.

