#### Primary Outcome

- fall rate per person at 6 months; as documented in care home falls record

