### 6.6.3 Loss to Follow-up

As the care home residents will be living in the participating care home, loss to follow-up is unlikely. If residents are transferred out of the care home then participation will end at date of transfer. Death is not considered as loss to follow-up in this study.

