#### **6.10.5 Analysis Population and Missing Data**

The primary analysis will be on the 'Intention-to-Treat' population, i.e. all those randomised and analysed according to the arm to which they were randomised.

It is likely that the proportion of missing data will be small. However, if the proportion of individuals with missing falls data is more than 5% a multiple imputation method (using baseline characteristics) will be used as the basis of a secondary sensitivity analysis.

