In Northern Ireland there is currently no primary legislation on capacity (according to the General Medical Council) and so decisions about medical treatment and care when people lack capacity must be made in accordance with the common law, which requires decisions to be made in a person's best interests. In Northern Ireland we will follow the procedures used in England.

The provision of informed consent to participate in the study includes consenting to data collection and to participating in study follow up as described in the protocol and the participant information sheet. Participants will be requested to consent to their medical records, including GP records, being accessed as part of the study and for supplementary data to be collected on their health service use.

The Principal Investigator (PI) at each University retains overall responsibility for the informed consent of participants at their site and will ensure that any person delegated responsibility to participate in the informed consent process is duly authorised, trained and competent to participate according to the ethically approved protocol, principles of Good Clinical Practice (GCP) and Declaration of Helsinki.

The right of a participant or consultee/WPoA to refuse participation without giving reasons will always be respected. The participant and their consultee/WPoA(S) as appropriate will remain free to withdraw from the study at any time without giving reasons and without prejudicing his/her further treatment and will be provided with a contact point where he/she may obtain further information about the study. The PI takes responsibility for ensuring that all vulnerable participants are protected and participate voluntarily in an environment free from coercion or undue influence.

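### Residents who move home leave follow-up because the intervention cannot follow them, a reason that is empty in the control arm and out of line with the rule for PIP withdrawal

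*Protocol*

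**What the plan says.** Section 6.6.2 deals with residents who move out of the home in which they were recruited: "they will be withdrawn, because it will not be possible for the intervention to be delivered elsewhere". It gives no other reason and makes no distinction by arm. It adds: "The data collected until the time at which they withdrew from the study, will be held and used". Section 6.6.3 repeats the cut-off: "If residents are transferred out of the care home then participation will end at date of transfer".

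Two other rules cover events that also stop the intervention, and they point in opposite directions:

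- **PIP withdraws and is not replaced (6.1.3.1).** Residents are told that the intervention has ended, but "the data will be collected for individual resident participants at standard data collection times".
- **Care home withdraws (6.1.3.3, written around the first month of resident recruitment).** Residents are told that "their care home has withdrawn and they can no longer take part in the study".

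The primary analysis (6.10.5) is by intention to treat: "all those randomised and analysed according to the arm to which they were randomised". The primary outcome (6.5) is "fall rate per person at 6 months; as documented in care home falls record". Mortality, hospitalisation and DBI are secondary outcomes in the same section. On record access, section 7.4 states: "Participants will be requested to consent to their medical records, including GP records, being accessed as part of the study". The primary-care questionnaire in Appendix 3 already extracts overnight hospital stays and prescribed medication from those records.

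**The concern.** Inability to deliver treatment is a reason to record that the intervention has ended. It is not in itself a reason to stop measuring outcomes. Control residents receive no PIP service, so for them the stated reason is empty, yet the rule removes them too. In the PIP-withdrawal case the protocol itself accepts that losing the intervention need not end data collection.

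Some of what is lost does not depend on the original home. Death, hospital admission and medication after a move can be read from the GP record, but once participation ends at transfer nobody looks. Routine collection of serious adverse events (6.11.2.1) runs through monthly contact with participating homes, so a later death or admission falls outside that route as well.

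Section 6.9.2 expects some residents to move. If moves reflect declining health, or occur at different rates by arm, the 6-month secondary outcomes are missing selectively. The documents do not say that moves are related to either. It is a plausible risk, not an established fact.

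**Working it through.** **1. Reproduce the planned size.** Inputs from section 6.8: falls rates 1.50 and 1.178 per person over 6 months, 44 clusters of 20, loss 20%, ICC 0.05, power 80%. A two-sided 5% test is assumed (6.10.4.1 pairs a 5% level with a 95% interval).

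- n per arm before clustering = (1.960 + 0.842)² × (1.50 + 1.178) / (1.50 − 1.178)² = 202.7
- design effect with 16 per cluster after loss = 1 + (16 − 1) × 0.05 = 1.75
- total = 2 × 202.7 × 1.75 / 0.8 = 887, against 880 planned
- power at 880: 352 per arm retained, effective n = 352 / 1.75 = 201.1, power 79.7%

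The plan's figure is reproduced.

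**2. How many residents the rule could touch.** Section 6.8 gives 33% mortality and 5% further loss over 12 months, and plans for 20% total loss at 6 months. The number of moves is not stated, so all non-death loss is treated as moves and the 12-month figures are halved.

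- From the 5%: 5% / 2 = 2.5%; 0.025 × 880 = 22 residents
- From the 20%: 20% − 33% / 2 = 20% − 16.5% = 3.5%; 0.035 × 880 ≈ 31 residents

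With moves spread evenly over 6 months, each loses half the follow-up on average. That is 2.5% / 2 = 1.25% to 3.5% / 2 = 1.75% of planned person-time.

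**3. Power if all of them were followed to 6 months.**

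| Non-death loss recovered | Retained per arm | Design effect | Effective n | Power |
|---|---|---|---|---|
| none | 352 | 1.75 | 201.1 | 79.7% |
| 2.5% | 440 × 0.825 = 363 | 1 + 15.5 × 0.05 = 1.775 | 204.5 | 80.3% |
| 3.5% | 440 × 0.835 = 367.4 | 1 + 15.7 × 0.05 = 1.785 | 205.8 | 80.6% |

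The gain is under 1 percentage point.

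**4. Illustrative bias in the falls rate ratio.** Assumptions, none of them from the documents: movers fall at twice the rate of stayers, 4% move in one arm and 1% in the other, and each mover loses half the follow-up. Set the stayers' rate to 1 in both arms, so that the only difference between arms comes from moves.

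- Full follow-up: rates 0.96 + 0.04 × 2 = 1.04 and 0.99 + 0.01 × 2 = 1.01; ratio 1.0297
- Falls exposure ending at the move: falls are 0.96 + 0.04 × 0.5 × 2 = 1.00 and 0.99 + 0.01 × 0.5 × 2 = 1.00; person-time is 1 − 0.02 = 0.98 and 1 − 0.005 = 0.995; ratio (1 / 0.98) / (1 / 0.995) = 1.0153
- Relative shift: 1.0153 / 1.0297 = 0.986, about 1.4%
- Counts per person with no exposure adjustment: ratio 1.00 / 1.00; 1 / 1.0297 = 0.971, about 2.9%
- Equal move rates in the two arms: no shift on either calculation

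The target effect is 1 − 1.178 / 1.50 = 21.5%.

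**5. Compare the rules.**

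| Event | Intervention continues? | Original home's falls record still in the study? | Data collection continues? |
|---|---|---|---|
| PIP withdraws, not replaced (6.1.3.1) | no | yes | yes |
| Care home withdraws (6.1.3.3) | no | no | no |
| Resident moves (6.6.2, 6.6.3) | no (never applied in control) | no | no |

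Access to the falls record would explain the pattern for falls. The protocol does not give that as its reason, and it would not explain dropping outcomes held in the GP record.

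**The case against.** A reader might infer that the rule contradicts the stated intention-to-treat analysis. It does not. Section 6.10.5 defines that population by randomisation and arm. Movers stay in it, are analysed as randomised, and contribute data up to the move (6.6.2). Section 6.8 expressly foresees partial follow-up. What is missing is observation after the move, which concerns the intention-to-treat principle and not the wording of the definition. For the same reason nothing already collected is thrown away.

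A reader might also treat section 6.1.3.1 as an exact parallel. It is not. When a PIP leaves, the resident still lives in an activated home whose falls record is the source of the primary outcome and whose staff can complete the proxy EQ-5D-5L. Care home withdrawal (6.1.3.3) is closer on access to records and takes the same line as the mover rule. This objection stands for falls and proxy measures. It does not reach mortality, admissions and medication, and it does not rescue a reason that is meaningless in the control arm.

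Obtaining falls from a home with no study agreement is harder than a telephone call, and ending falls exposure at the move is in substance what the plan already does. GP-record data may also be out of reach once a resident changes practice. These limits stand and shape the fix.

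**Conclusion.** The point holds as an inconsistency and an avoidable loss of secondary-outcome data. Follow-up of movers ends for a treatment-delivery reason that does not apply to half the trial and that section 6.1.3.1 does not follow. As written, 6-month mortality, hospitalisation and DBI go unobserved for residents who move, although the route to these data and the consent for it are in place.

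The size is modest: about 22 to 31 of 880 residents. This rests on treating all non-death loss as moves and on halving the 12-month figures. Power changes by less than 1 percentage point. A reader might infer a material bias in the primary result, but the documents do not support that. The shift of about 1.4% needs an arm imbalance and a doubled fall rate that the protocol does not suggest, and it is small beside the 21.5% target. Whether the loss is informative cannot be settled from the documents.

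This is a cheap improvement worth making. It does not threaten the primary analysis.

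**What to change.** Separate two events in the protocol: intervention no longer delivered, and end of follow-up.

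- For a resident who moves, record the date and reason and mark the intervention as ended (intervention arm). Unless consent is withdrawn, keep the resident in follow-up in both arms.
- At 6 months, take vital status, hospital admissions and medication (for DBI) from the GP record, where the resident remains with the practice or the record can still be accessed. Section 7.4 already provides for consent to this, and Appendix 3 already extracts admissions and medication. Check that the consent wording covers access after a move.
- Censor falls exposure at the move date. Use falls from the receiving home only if readily obtainable.
- Reconcile sections 6.1.3.1, 6.1.3.3, 6.6.2 and 6.6.3, so that each says separately what happens to the intervention and to each source of data.

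The cost is a protocol wording change and a record look-up for roughly 20 to 30 residents. The downside is incomplete data for those who change GP practice, which should be reported by arm.

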### 6.6.3 Loss to Follow-up

As the care home residents will be living in the participating care home, loss to follow-up is unlikely. If residents are transferred out of the care home then participation will end at date of transfer. Death is not considered as loss to follow-up in this study.

### 6.6.4 Study Closure

The study ends four months after the end of data collection of last phase of recruitment.

## 6.7 Randomisation

The study is a 2-arm cluster-randomised controlled trial, which will recruit using recruitment triads. A recruitment triad (i.e. the randomised cluster) consists of 1 GP practice plus 1 PIP plus a mean of 20 residents from at least one care home. Following recruitment of the triad, it will be randomised to either the intervention or control groups. Randomisation will be performed using a web-based electronic randomisation system integrated into the study database.

Figure 2. Study flow chart

[figure not shown]

## 6.8 Sample Size

A sample size of 880 (440 in each arm) would detect a decrease in fall rate from 1.50 per individual over 6 months to 1.178 with 80% Statistical Power. This assumes that the number of clusters available will be 44, with a mean of 20 participants from each, a loss rate of no more than 20% and an ICC of 0.05 or less.

To balance any under recruitment with over recruitment (eventually balancing out over the whole study), we will recruit in all triads a mean of 20 participants. Any variation with these limits would need to be approved by TSG and or DMC.

These assumptions are based upon data from the CAREMED (29) study, which estimated a fall rate of 1.5 per individual over a 6 months period. The detectable difference (from 1.5 to 1.178) is a relative reduction of 21% which is half that detected within a UK based pharmacist led medication review service provided to care homes.

Data from the CAREMED (29) trial indicated a mortality rate of 33% and further loss to follow-up of 5% over 12 months. Thus, a reasonable estimate of total losses due to mortality or other reasons over 6-months would be 20%. However, we will use data, where possible, up to the point at which someone withdraws from the study (either voluntarily, or otherwise). Therefore, those lost to follow-up, for whatever reason, should contribute some information on falls rate to the study analysis.

## 6.9 Recruitment and Retention

### 6.9.1 Recruitment

We will recruit a total of 44 triads; each triad will consist of 1 GP + 1 PIP + a mean of 20 care home residents, from at least 1 care home. Recruitment will be in sequential phases: Pilot, Phase 1, Phase 2 and Phase 3 (see diagram 3 below). Each of these phases encompasses all elements of the study – identification, recruitment and formation of the triads (GP, PIP and care home/s), recruitment of resident participants, randomisation and PIP training for the intervention group.

It is envisaged that recruitment will be equal across all four locations, but some variation across locations is expected.

**Figure 3. Pilot and RCT recruitment numbers flow chart by phase and location**

[figure not shown]

---

#### **6.9.1.1 PIP recruitment**

44 PIPs will be recruited, concurrently with the GP practice with whom they should ideally have an already established close working relationship.

#### **6.9.1.2. GP practice recruitment**

Recruitment and consent will be complex due to the need to identify medical practices, recruit homes and then residents.

Ideally, there will be sufficient PIPs expressing an interest in the study, with already established close working relationships with a GP practice. These practices will be approached by local researcher and invited to take part. We will ask for basic demographic information about interested GP practices and their linked care home (e.g. the resident mix and home ownership), so that in the event of excessive interest, we may purposively sample. However, if this does not provide sufficient GP practices, then we will use relevant local research networks and contact medical practices in the area, with a link to care homes, with information about the study and seek expressions of interest.

#### **6.9.1.3 Care home recruitment**

The participating GP practice will approach one (or more, if necessary) of their eligible care homes and invite them to take part in the study. Recruitment via the medical practice has been successful in our previous studies, and in the Feasibility Study, and was recommended by care home managers at a PPI meeting. If the care home manager expresses an interest, they will be sent a formal invitation pack by the local researcher (including letter and information sheet). If a care home declines participation, the GP will contact another home and invite them to participate. If there are insufficient residents in one home, then a second home will be recruited.

Where a home does not wish to participate, and there is no alternative home, a different GP practice in that area will be identified and recruited and the process to recruit the care home(s) will be repeated.

#### **6.9.1.4 Resident recruitment**

Once we have recruited participating medical practices, PIPs and care homes, GPs will identify, and randomly list, their registered patients resident in the identified care homes taking  $\geq 1$  medication. The GPs will screen the list against the study inclusion and exclusion criteria and record reasons for exclusion; this data will be collected by the local researcher. The GP practice will send an invitation letter, information sheet (spoken version if necessary) and consent form to each eligible resident in their care, or in the case of residents who the manager knows lacks capacity, to their next of kin. The letters will be sent via the care home managers who will deliver the letters to residents (or in the case of residents who the care home manager knows to lack capacity, post them to their next of kin). The care home manager will visit each resident after at least 24 hours, and obtain verbal consent for the local researcher to be allowed to approach them to discuss participation in the study.

To ensure the recruitment procedure is not biased disproportionately including either those with, or those without, capacity we will ask the care home manager to use the list prepared by the GP and residents will be approached according to the order of the GP list.

The local researcher (see 1.4.3) will then visit the care home and meet with interested residents. They will undertake a brief assessment to determine capacity with residents, using a Capacity Assessment for Residents form, based on a validated tool [5], then obtain fully informed consent from those with capacity, who are willing to participate.

The study will recruit residents both with and without capacity because this is representative of care home populations, where many residents are without capacity, and to exclude such residents would render the research ungeneralizable. In addition, all residents could benefit from the intervention, and so residents without capacity should not be denied the opportunity to participate. For a more detailed justification, please see Appendix 4.

For full details of the procedure for those who lack capacity, taking into account differences in legislation across devolved home nations, please see Section 7.4.

If someone loses capacity during the six months of the study, they will remain in the study. This is one of the points to be agreed in the Consent Form: "I agree to continue participating in the study if I lose capacity before the end of the study". If someone does lose capacity during the course of the study, they will be consented again with a consultee, or WPoA who will be identified in the same manner as described in Section 7.4.

At each follow up visit, the care home manager will be asked if any participants have re-gained capacity. Should anyone regain capacity during the course of the study, we would go through the Patient Information and Consent Form, and if the resident is willing, re-consent them. In Scotland this would be done using the template Resident Recovered Capacity documents, and in England it would be with the original Patient Information and Consent.

Figure 4. Care home resident recruitment flow chart

[figure not shown]

---

### 6.9.2 Retention of participants

The intervention will be delivered over a period of six months, during which time we do not expect many participants to drop out. However, it is likely that, due to the age and frailty of the population and based on our experience in previous studies, some of our participants may die in the six months intervention period and some may move. In either case, all data will be collected up to the end of the participant's study participation. However, if a participant dies, or withdraws, before the intervention has begun, then they can be replaced.

If a participant is excluded, as a post randomisation exclusion, they may be replaced, if this can be done within two weeks of the beginning of the intervention.

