### **6.1.3.4 Residents of the consented GP practice who are resident in the care home.**

If a resident chooses to leave the study prematurely the primary reason for discontinuation will be determined and recorded, if at all possible. Withdrawn participants will not be replaced, unless they withdraw before the start of the intervention. Residents will be made aware (via the information sheet and consent form) that should they withdraw, the data collected to date cannot be erased and may still be used in the final analysis.

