### 6.3.1 Eligibility Criteria for Prescribing Independent Pharmacist (who will deliver the intervention)

#### 6.3.1.1 Inclusion criteria:

- registered as a pharmacist independent prescriber
- following CHIPPS study training, can demonstrate to their mentor and independent GP assessor competence to deliver service specification
- ability to work flexibly and commit a minimum of 16 hours a month to deliver the service for six months

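### Residents can be replaced after their triad has been randomised, so part of the trial population can be recruited with allocation known

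*Protocol*

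**What the plan says.** **Order of events.** Protocol 6.7 defines the randomised cluster as a triad that "consists of 1 GP practice plus 1 PIP plus a mean of 20 residents from at least one care home", and continues: "Following recruitment of the triad, it will be randomised to either the intervention or control groups". Section 6.9.1 lists the steps of each recruitment phase in the same order, ending with "recruitment of resident participants, randomisation and PIP training for the intervention group". Residents are thus in place before allocation.

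**Replacement.** Three statements set the cut-off:
- 6.1.3.4: "Withdrawn participants will not be replaced, unless they withdraw before the start of the intervention".
- 6.9.2, on death or withdrawal: "if a participant dies, or withdraws, before the intervention has begun, then they can be replaced".
- 6.9.2, next sentence, on a participant who is "excluded, as a post randomisation exclusion, they may be replaced, if this can be done within two weeks of the beginning of the intervention".

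**Who recruits.** Under 6.9.1.4 the GP lists registered residents in random order and screens them. The home manager makes the first approach in list order, and the local researcher assesses capacity and takes consent. Under 6.10.1 the local researcher also collects the outcome data.

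**Analysis population.** Section 6.10.5 defines the primary, intention-to-treat population as "all those randomised and analysed according to the arm to which they were randomised".

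**The concern.** In a cluster trial that staff cannot easily be kept blind to, completing resident recruitment before allocation is the main protection against selection bias. The protocol adopts that order, then sets the replacement cut-off at the start of the intervention instead of at randomisation. Between those two dates, people who know the allocation can bring new residents into a triad.

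The protocol describes no masking of those people, and masking would be hard to achieve. The PIP is based at the practice (Appendix 2, section 2) and visits or contacts both practice and home about weekly (6.4). Screening includes a judgement on end-of-life status, and only about 55% of those invited are expected to consent (footnote to 6.3.2.1). There is therefore room for both staff discretion and self-selection once the arm is known.

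At stake is the comparability of the arms on fall risk, which is the primary outcome. It is also unclear whom the primary analysis contains, since a resident who was absent when the triad was randomised has no clear place in the 6.10.5 definition.

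**Working it through.** **1. The sections side by side.** The sequence in 6.7 and 6.9.1 is residents recruited, triad randomised, intervention PIPs trained, intervention begins. The rule in 6.1.3.4 and the first rule in 6.9.2 are open until the last step. Part of their window may precede randomisation, where replacement is harmless. The second rule in 6.9.2 applies only after randomisation by its own terms, so replacement after allocation is expressly allowed. Section 6.9.1.4 does not say that replacements must be taken in order from the list made before allocation.

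**2. The plan's own sample size.** Inputs from 6.8: rates 1.50 and 1.178 falls per person over 6 months, 80% power, 44 clusters of 20, 20% loss, ICC 0.05. The 5% level is from 6.10.4.1; two-sided testing is assumed.
- Effective n per arm = (1.96 + 0.8416)² × (1.50 + 1.178) / 0.322² = 202.7.
- Retained cluster size = 20 × 0.8 = 16; design effect = 1 + 15 × 0.05 = 1.75.
- 202.7 × 1.75 / 0.8 = 443.5, so 444 per arm and 888 in total, against the stated 880.
- Power at 880: 352 / 1.75 = 201.1 effective per arm; SE = √(2.678 / 201.1) = 0.1154; 0.322 / 0.1154 − 1.96 = 0.83; power 79.7%.

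The stated design reproduces and is not in dispute.

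**3. How many residents might become replaceable.** Section 6.8 cites 33% mortality and a further 5% loss over 12 months. The interval g from randomisation to start is not stated; 0.5 to 3 months is assumed. With a constant hazard, leavers = 880 × (1 − 0.67^(g/12)) for deaths, and 0.62 replaces 0.67 for all losses.

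| g (months) | Deaths | All losses | Share of 880 |
|---|---|---|---|
| 0.5 | 14.6 | 17.4 | 1.7–2.0% |
| 1 | 28.9 | 34.4 | 3.3–3.9% |
| 2 | 56.8 | 67.4 | 6.5–7.7% |
| 3 | 83.8 | 99.1 | 9.5–11.3% |

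Post-randomisation exclusions would add to these; their number cannot be derived.

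**4. Illustrative bias with no true effect.** Suppose a share r of one arm is replaced by residents with k times the fall rate, and the other arm is unchanged. Both r and k are assumptions. Then λ₂ = 1.50 × (1 − r + rk), rate ratio = 1 − r(1 − k), SE = √((1.50 + λ₂) / 201.1), d = (1.50 − λ₂) / SE, and type I error = 1 − Φ(1.96 − d) + Φ(−1.96 − d).

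For r = 5% and k = 0.5: λ₂ = 1.4625, SE = 0.1214, d = 0.309, type I error 6.1%.

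| r | k = 0.75 | k = 0.5 | k = 0.25 |
|---|---|---|---|
| 2% | 0.995; 5.0% | 0.990; 5.2% | 0.985; 5.4% |
| 5% | 0.9875; 5.3% | 0.975; 6.1% | 0.9625; 7.5% |
| 10% | 0.975; 6.1% | 0.950; 9.5% | 0.925; 15.6% |

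(Each cell: rate ratio; type I error.)

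**5. Power if replacement ends at randomisation.** Let f be the fraction still present at the start. Then m = 16f and effective n per arm = 22m / (1 + (m − 1) × 0.05). For one month, deaths only: f = 0.967, m = 15.48, n = 197.5, power 79.0%.

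| g (months) | Power, deaths only | Power, all losses |
|---|---|---|
| 0.5 | 79.3% | 79.3% |
| 1 | 79.0% | 78.8% |
| 2 | 78.2% | 77.9% |
| 3 | 77.5% | 77.0% |

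**The case against.** **Mitigation.** The random list and list-order approach in 6.9.1.4 limit choice, and replacements may in practice have followed it. The primary model adjusts for baseline fall rate (6.10.4.1), which would absorb part of any imbalance. Both points stand as mitigation. The protocol does not extend the list rule to replacements, however, and adjustment reaches only what baseline falls capture.

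**Masking and size.** Absence of masking is inferred from silence, and the interval may appear in the timeline or flow figures, which are not shown. A constant hazard may overstate early deaths, because residents receiving end-of-life care are excluded. The illustration also needs selection in one arm only. All of this is fair: the size is unknown, and at 2% replaced the effect is small.

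**Intention to treat.** The unit randomised is the cluster, and adding a resident does not remove the one replaced. This is therefore an unresolved classification of newcomers, not a flat contradiction.

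Stronger readings that the document does not support:
- *A reader might infer that early deaths vanish from mortality.* Nothing says a replaced resident's data are deleted. Figure 1 in 6.6 records serious adverse events from enrolment; 6.11.2.1 defines these as death and hospitalisation and collects them monthly in both arms. Section 6.1.3.4 says data already collected cannot be erased.
- *A reader might infer that the rule cannot run alike in controls.* Figure 1 labels its common baseline time point as the start of intervention, and that point can serve control triads.
- *A reader might infer that a failed PIP assessment makes a triad ineligible in one arm.* A PIP inclusion criterion is that the pharmacist, "following CHIPPS study training, can demonstrate to their mentor and independent GP assessor competence to deliver service specification", and 6.9.1 lists that training after randomisation for the intervention group. But the protocol states no consequence of failure, and 6.1.3.1 has resident data still collected after a PIP withdraws.

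**Conclusion.** The point holds as a design weakness in the replacement rules. As written, 6.1.3.4 and 6.9.2 permit residents to be recruited into a triad after its allocation is known. No masking of the recruiters is described, replacements need not follow the pre-allocation list, and newcomers have no defined place in the primary population.

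The size of any bias cannot be determined from the protocol. With half the fall rate among replacements in one arm only, the spurious rate reduction is 1%, 2.5% or 5% for 2%, 5% or 10% replaced. Against the planned reduction of 21.5% (1 − 1.178/1.50), that is about 5%, 12% or 23% of the target effect. These figures rest on the assumed share, relative rate and one-sided selection, and ignore baseline adjustment. They show that a short gap with few replacements does little harm and that a long one could matter. They do not show that bias occurred. The case for change is that the opening is avoidable at little cost.

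**What to change.** - In 6.1.3.4 and 6.9.2, allow replacement of a resident only before the triad is randomised, and delete the provision for replacing post-randomisation exclusions.
- In 6.10.5, state that every resident enrolled when the triad was randomised stays in the intention-to-treat set, with deaths and withdrawals counted from randomisation.
- Leave any resident added after allocation out of the primary analysis. Report the number of such additions by arm, and include them in a sensitivity analysis.

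The change is to wording only. Its price is a modest loss of numbers, which should be counted on top of the 20% allowance and not within it: 6.8 derives that 20% from six-month losses, and the cited 38% over 12 months already gives 1 − 0.62^0.5 = 21.3% over six. Power would be about 79% for an assumed one-month gap and about 77% for three months, against 79.7%. Keeping the interval from randomisation to start short limits the loss.
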